### Participants

#### Study 1

The epidemiological study includes all persons hospitalized at the three specialized SCI departments in Norway for primary rehabilitation from 1 January 2004 to 1 January 2014. All relevant persons identified will receive a questionnaire focusing on past and present PUs (Table 1). The study will run from January 2017 to May 2018 (Fig. 1).

#### Study 2

Sixty persons with SCIs and ongoing PUs, as well as their relatives and local caregivers, will be included in a RCT (Fig. 1). The participants will be randomized into two groups with 30 persons in each group. One group, their relatives and local caregivers will be offered regular, interdisciplinary, outpatient follow-up by the SCI department’s wound team at Haukeland University Hospital and at Sunnaas Rehabilitation Hospital via videoconferencing, telephone, and consultations at the outpatient wound clinic at the hospital (the teleSCI group). The other group, their relatives and local caregivers will receive guidance by the SCI department’s wound team at Haukeland University Hospital or Sunnaas Rehabilitation Hospital, based on existing routine. The follow-up will be offered by telephone and visits at the outpatient wound clinic at the hospital, based on request from the local caregivers or the patient. (the usual care group). The RCT will run from June 2015 to July 2019 (Fig. 1).

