### Randomization and allocation concealment

Participants in the RCT will be randomized directly after baseline assessment to group 1 (the teleSCI group) or to group 2 (the usual care group). The randomization will be stratified with respect to the hospitals, blocked with varying sizes, and carried out by use of the random-number generator in the statistical software SPSS. The randomization sequence list will be created in advance of recruitment, by an experienced scientist who is not a member of the research team. The randomization numbers will be provided in closed and sealed envelopes, unavailable to those who enroll the participants. At least two persons, either investigators or other medical staff members, will be present to secure the allocation procedure. If the participant is included in the teleSCI group, further arrangements for the installation of the telerehabilitation software and training in the use of the software program and equipment will be addressed to the participant, the relatives, and the local caregivers.

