##### Primary endpoints

Study 2 will focus on the effect of using teleSCI compared with other outpatient approaches in the follow-up of persons with PUs after a SCI, measured in terms of percentage wound size healed, and the time to heal. A systematic evaluation of the ulcer will be done, using the validated Time Infection Moisture Edge (TIME) form [26] and the Photographic Wound Assessment Tool (PWAT) scale [27], where the amount of fibrin and granulation tissue present, percentage of epithelialization of the wound, percentage of moisture present, and the appearance of the wound edges will be described. Time to heal will be measured counting days until healing, or measuring the amount of healing at the end of the 12-month follow-up period. Changes in self-reported health-related quality of life (HRQoL) and the need for assistance will be compared using the 12-item Short Form Health Survey (SF-12v) [28], the Five Dimensions European Quality of Life scale (EQ-5D) [23], and the International Spinal Cord Injury Quality of Life questionnaire (ISCI-QoL) basic data set [29]. The SF-12v [28] measures functional health and well-being from the patient’s point of view. The EQ-5D scale [23] measures mobility, self-care, activities, pain, discomfort, and anxiety/depression. The participants perform a self-rating of their health in a box-scale and on a vertical visual analog scale. In the ISCI-QoL questionnaire [29], the participants will rate their physical and psychological health, using a box-scale. The SF-12v [28], EQ-5D [23], and ISCI-QoL [29] will be used as a quantitative measure of the health outcome that reflects the participant’s own health judgment before and, at the end of, the follow-up period. The Spinal Cord Independence Measure, version III (SCIM III) scale [24] has been designed specifically for persons with SCI and is a comprehensive ability-grading scale, focusing on the ability of performing basic tasks, and the effect the SCI has on the overall medical condition and comfort. SCIM III [24] will be rated at baseline and at the end of the follow-up period, and the results from both groups in the RCT will be compared with focus on changes in performing ability during the follow-up period.

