### Sample size

For the demonstration of effect between the two groups, sample size calculation is based on an expectation of a standardized difference of at least 0.8 (typically considered a large effect). With 80% power, we will need 25 participants in each of the two groups hence we include 30 in each group to tolerate some drop outs.

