### Statistical analysis

Data from the end of the study will be analyzed using chi-square tests for categorical data and *t* tests for continuous data. Regression analyses (linear and logistic) will be performed to make any necessary adjustments for baseline differences. In addition, we will also analyze developments over time in the two groups, using the mixed-models analysis.

Mean QoL scores with corresponding 95% confidence interval will be estimated in each of the two treatment groups, and the groups will then be compared using *t* tests and mixed-models analysis. A cost-benefit analysis will be carried out to assess the cost of outpatient treatment via telemedicine, compared with outpatient treatment at the hospital.

The reduction (in percentage) of PU size is calculated with corresponding 95% confidence interval for each of the two treatment groups. The groups will be compared with regard to percentage reduction in ulcer size, using *t* tests and mixed models. All quantitative statistical analyses will be performed using the SPSS and STATA statistical software package. Computer Assisted Qualitative Data Analysis (CAQDAs) will be used in the qualitative analysis.

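### The wound-size comparison has no named primary model, makes covariate adjustment depend on observed imbalance, and leaves out the hospital stratum; fixing the model in advance is a free improvement

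*Protocol article*

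**What the plan says.** All references are to the protocol article.

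- **Randomization and allocation concealment:** "The randomization will be stratified with respect to the hospitals, blocked with varying sizes". Study 2 has two hospitals.
- **Primary endpoints:** the effect is "measured in terms of percentage wound size healed, and the time to heal".
- **Statistical analysis:** end-of-study data are compared by chi-square and t tests, and then "Regression analyses (linear and logistic) will be performed to make any necessary adjustments for baseline differences". Mixed models are added for development over time. Percentage reduction in ulcer size is to be compared by t tests and mixed models, named side by side. The section does not rank them, list covariates, define when an adjustment is necessary, or mention hospital.
- **Sample size:** "With 80% power, we will need 25 participants in each of the two groups", for a standardized difference of 0.8, "hence we include 30 in each group to tolerate some drop outs".
- **Methods/design and Table 1:** wound size is measured at every assessment. The quality-of-life instruments and SCIM III are recorded at baseline and at the end of follow-up.

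**The concern.** In a randomized trial, baseline differences arise by chance. The reason to adjust for a variable is that it predicts the outcome, and that is known before any imbalance is seen. A rule that waits for an imbalance therefore selects covariates on the wrong ground. The rule is stated in the text, so an unseen analysis plan would have to replace it rather than fill it in.

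Two further points follow. The trial stratified by hospital, but the named t and chi-square tests discard that factor. And for one wound outcome the text allows a t test, a regression if thought necessary, and a mixed model, with none ranked first. At stake are precision in a trial of 60 people powered only for a large effect, and freedom to choose among results.

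**Working it through.** **Inputs.** From the Sample size section: standardized difference d = 0.8, power 80%, 25 evaluable and 30 planned per arm. Assumed: two-sided alpha of 0.05 (not stated, but it reproduces the 25), and d applied to percentage reduction in ulcer size (the section names no outcome). Also assumed, as a range: R2, the share of outcome variance explained by hospital plus baseline ulcer size.

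**1. The plan's own figure.** n per arm = 2 × ((1.960 + 0.842)/0.8)² = 24.53, rounded up to 25. This reproduces the stated figure, and it corresponds to an unadjusted two-group comparison. Power at 25 per arm is 0.807 (normal approximation) or 0.791 (noncentral t). At 30 per arm it is 0.873 or 0.861.

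**2. Power with the covariates in the model.** The residual SD becomes sqrt(1 − R2), so power = Φ(0.8 × sqrt(25/2)/sqrt(1 − R2) − 1.96). For R2 = 0.20 this is Φ(2.828/0.894 − 1.96) = Φ(1.20) = 0.885. The last column is the difference detectable with 80% power, 2.802 × sqrt(1 − R2) × sqrt(2/25).

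| R2 (assumed) | Power, normal | Power, noncentral t (46 df) | Detectable difference (SD) |
|---|---|---|---|
| 0 | 0.807 | 0.791 | 0.79 |
| 0.05 | 0.827 | 0.811 | 0.77 |
| 0.10 | 0.846 | 0.831 | 0.75 |
| 0.20 | 0.885 | 0.872 | 0.71 |
| 0.30 | 0.922 | 0.911 | 0.66 |

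**3. What each way of choosing the model does.** Simulated trials with 25 per arm and two hospitals (26 and 24 participants, split equally within each). Hospital explains 5% of variance; baseline size explains 10%, 25% or 40% (all assumed). There were 20,000 replicates under no effect and 5,000 at d = 0.8. The trigger was read as follows: use the adjusted model only when a t test on baseline size gives p < 0.05.

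| Procedure | Type I error at 10 / 25 / 40% | Power at 10 / 25 / 40% |
|---|---|---|
| t test, unadjusted | 0.043 / 0.044 / 0.044 | 0.792 / 0.792 / 0.802 |
| Adjusted model, fixed in advance | 0.048 / 0.051 / 0.052 | 0.845 / 0.900 / 0.958 |
| Adjust only if baseline test significant | 0.041 / 0.039 / 0.034 | 0.795 / 0.802 / 0.818 |
| Report whichever of the first two is significant | 0.060 / 0.070 / 0.078 | not a legitimate comparison |

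In the 25% column, fixed adjustment gains 0.900 − 0.792 = 0.108 in power. The trigger gains 0.802 − 0.792 = 0.010, about a tenth of that.

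**The case against.** The strongest reply is that much of this is silence in a condensed article. Mixed models and regressions are named, their covariates are unstated rather than excluded, and a separate analysis plan may list them. That stands as far as the covariate list goes. It does not cover the stated trigger, or the two methods named for one outcome without a ranking.

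Three stronger readings are tempting and not supported:

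- A reader might infer that the wound outcome rests on an unadjusted t test alone. Mixed models are named in the same sentence, which widens the choice of model rather than closing it.
- A reader might infer that baseline ulcer size is ignored. It is the denominator of the percentage reduction, and a model of development over time would ordinarily use the baseline measurement. Dividing by baseline is still not covariate adjustment, since it does not remove the remaining dependence of percentage reduction on initial size.
- A reader might infer that the quoted rule inflates the error rate. It ties adjustment to baseline differences, not to outcome results; applied strictly as simulated, its type I error was 0.034 to 0.041. The 6 to 8% figure needs someone to pick the better result, which the document neither states nor proposes.

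It is also fair that the t test errs on the conservative side, that the gain is small if R2 is near 0.05, and that with all 30 per arm retained unadjusted power is already about 0.86.

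**Conclusion.** The point holds as a free improvement. The plan leaves the primary model for the wound outcome open, adjusts on an inferior criterion and does not carry the stratification factor into the analysis. Neither the sample size figure nor the validity of the t test is in question.

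At 25 per arm, the normal-approximation power gain over 0.807 is about 0.02 to 0.04 for R2 of 5 to 10%, and about 0.08 to 0.11 for R2 of 20 to 30%. These figures rest on a two-sided alpha of 0.05, a roughly normal outcome and an R2 that the document does not supply. The finding that a trigger forgoes most of the gain rests on one reading of an undefined word: a 5% significance test on baseline size. The open choice of model remains whatever R2 is.

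**What to change.** In the Statistical analysis section:

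1. Name one primary model for percentage reduction in ulcer size, either a linear model at the end of follow-up or a mixed model. Include treatment, hospital and log baseline ulcer area as fixed covariates, whatever imbalance is observed.
2. For the quality-of-life scores and SCIM III, use the same form with the baseline score of that instrument.
3. Where no baseline value exists (satisfaction and participation, costs, consultation counts), adjust for hospital only.
4. Delete the conditional adjustment for baseline differences, and keep the unadjusted t test as a sensitivity analysis.

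The cost is a few sentences. Hospital is known from randomization and the baseline measurements are already planned, so no new data or participants are needed. The Trial status section places the start of trial data entry in autumn 2018 and speaks of it as still to come, so at that date the model could have been fixed before the outcome data were assembled.

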## Methods/design

This research project consists of study 1 and study 2. The design of study 1 is a national multicenter trial, where epidemiological data of SCIs and PUs in Norway from 1 January 2004 to 1 January 2014 will be analyzed. A prevalence analysis of PUs will be performed. A statistical analysis will reveal possible risk factors for PUs after SCI.

Individuals with SCI and present PUs will be invited to participate in study 2, which is a randomized controlled pilot trial (RCT). The participants will be randomized into two groups, where one group and their local caregivers will be offered regular, interdisciplinary, outpatient follow-up by a wound team via videoconferencing, outpatient appointments at the hospital and telephone (the teleSCI group). The other group and their local caregivers will receive guidance based on existing routines, by telephone or by outpatient appointments at the hospital (the usual care group). The only difference between the follow-up in the two groups will be that the teleSCI group will be followed by regular outpatient videoconferencing consultations from the patient’s home. The interdisciplinary wound team at the SCI departments consists of a physician, a wound nurse and an occupational therapist. A plastic surgeon and an orthopedic surgeon will be supporting when needed. The local caregivers consist of local home-care nurses, and next of kin. Both groups of patients will be followed until healing of the PU, or for a maximum of 12 months (Figs. 1 and 2). A systematic and holistic evaluation of the patient will be done at baseline. A custom made journal will be used at baseline and during the follow-up period to evaluate the treatment applied. QoL and functioning will be mapped at baseline and at the end of the follow-up period. The wound size will be measured at every assessment, using validated forms and scales. Technical logistics and costs of the health care services delivered will be mapped and evaluated using custom-made forms at every assessment. In addition, a user satisfaction and participation form will be registered either when the ulcer is healed, or after a maximum of 12 months’ follow-up (Table 1). The results from the two groups will be compared with focus on ulcer healing, QoL, user participation, and satisfaction and cost-benefit. A selection of participants in the RCT study will participate in a semi-structured interview about their experiences in the follow-up (Fig. 2 and Table 1).

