*How*: using videoconferencing and remote control software to a laptop at the patient’s location	
*Where*: from Haukeland University Hospital and Sunnaas Rehabilitation Hospital to the patient’s home	
*When/how much*: the experimental intervention consists of pressure ulcer treatment guidance every second or third week until the pressure ulcer has healed, or a maximum of 52 weeks.	

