##### Secondary endpoints

The health care services as well as patient satisfaction and participation in both groups will be measured and evaluated using customized questionnaires.

In the cost-benefit form we will ask for time used at each consultation, travel distance to drive to and from the outpatient clinic at the SCI departments, as well as time used to travel, and distance driven for the local caregivers to and from the participants’ home. The number of caregivers participating in each session will be recorded, together with the total number of consultations for each participant, including teleSCI consultations, outpatient appointments at the hospital and telephone calls. Loss of working time for the participant and for any caregivers will be recorded, and so will medication and bandages used in every treatment session, both at the hospital and at home. CO_2_ emissions and costs for the environment will be mapped at every session.

Any technical problems will be mapped at every session. A custom-made questionnaire about the user’s experience with the follow-up will be mapped at the end of the follow-up period. This form contains questions about sufficient information provided before the inclusion, and during the follow-up period, as well as the participants’ experience regarding the follow-up. The results from the two groups will be compared with focus on differences in the user participation and satisfaction.

The investigators at the SCI departments at Haukeland University Hospital and Sunnaas Rehabilitation Hospital will supervise the filling in of the questionnaires and forms. After the conclusion of the follow-up period, a sample of participants will be requested to participate in a semi-structured qualitative interview based on the participants’ observation and experience.

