### The teleSCI group

The participants with SCI and PU (*n* = 30) and their local caregivers will be offered interdisciplinary outpatient follow-up every second or third week, provided by the specialized SCI department’s wound team via videoconferencing. The follow-up will consist of teleSCI appointments, visits to the SCI outpatient wound clinic at the hospital and telephone consultations. The Template for Intervention Description and Replication (TIDieR) [31] Checklist and Guide (Table 2) has been used to record and describe the intervention by teleSCI. This will secure treatment fidelity, replication for future trials, and transparency of reporting the results.

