### The usual care group

The participants with SCIs and PUs (*n* = 30) and their local caregivers will receive guidance based on existing routines provided by the specialized SCI department’s wound team. Telephone contact and appointments at the SCI outpatient wound clinic will be based on initiative taken by the local health care service/patient/next of kin. As usual, as care services vary in type and frequency, the follow-up provided for each participant will depend on the local resources available.

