### Technical solutions [32]

In this project, we use the term “teleSCI” about computer-based videoconferencing with remote webcam and the use of telephones [33–35].

The technical solution is in line with the “Sunnaas model of telerehabilitation” [36, 37], with has also been used in other research projects concerning telerehabilitation at Sunnaas Rehabilitation Hospital [11, 32]. Based on the experiences from these projects, videoconferencing guidelines have been established at the hospital [33–35].

We will use Cisco Meeting/Acano videoconference software, and videoconferencing equipment installed at the outpatient clinic at the SCI departments at Haukeland University Hospital and at Sunnaas Rehabilitation Hospital. Participants will be given a webcam for the duration of the project. The camera will be connected to either the participant’s laptop or to a project laptop, containing downloaded, encrypted videoconferencing software (Cisco Meeting/Acano) delivered by the Norwegian Health Net (NHN). This is a company owned by the Ministry of Health and Care services in Norway. The encrypted software meets requirements with regards to data safety aspects, privacy, and confidentiality [19]. As the therapy sessions are live, there are no recordings or storage of video, sound or picture. The project wound nurse and a technician will be available to support and assist the participants should technical problems arise.

Our current technical setup builds upon experience from the feasibility study [11]. To maintain safety aspects, a checklist has been implemented to be used at the start of each therapy session to control and adjust the patient’s physical environment [34]. This is to ensure optimal follow-up conditions, preserve accurate procedures in case of emergency and to accommodate privacy issues. Technical errors will be logged in each consultation.

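### The economic comparison is worded by mode of delivery rather than by randomised arm, and the itemised cost list has no line for teleSCI equipment, set-up and technical support

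*Protocol article*

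**What the plan says.** The Statistical analysis section defines the economic comparison in one sentence: "A cost-benefit analysis will be carried out to assess the cost of outpatient treatment via telemedicine, compared with outpatient treatment at the hospital". Methods/design describes the comparison differently: "The results from the two groups will be compared with focus on ulcer healing, QoL, user participation, and satisfaction and cost-benefit".

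The arms are mixed in content. For teleSCI: "The follow-up will consist of teleSCI appointments, visits to the SCI outpatient wound clinic at the hospital and telephone consultations". Table 2 sets the frequency: "the experimental intervention consists of pressure ulcer treatment guidance every second or third week until the pressure ulcer has healed, or a maximum of 52" (the unit is weeks). For usual care: "Telephone contact and appointments at the SCI outpatient wound clinic will be based on initiative taken by the local health care service/patient/next of kin".

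The Secondary endpoints section describes the cost form, beginning "In the cost-benefit form we will ask for time used at each consultation, travel distance to drive to and from the outpatient clinic". It goes on to caregiver travel, number of caregivers, each participant's total number of consultations (video, hospital and telephone), lost working time, medication, bandages and CO2. Technical solutions adds resources that only the video arm uses: "Participants will be given a webcam for the duration of the project", with a project laptop where needed, encrypted software, clinic videoconferencing equipment, and support from a technician and the wound nurse. Randomization and allocation concealment adds software installation and user training for participants allocated to teleSCI.

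**The concern.** The Statistical analysis section compares quality of life and ulcer size between the two treatment groups. Only the cost sentence switches to a contrast between modes of delivery. The cost hypothesis does the same, setting teleSCI against traditional hospital treatment. An analyst who took this literally could set video sessions against hospital visits. That would drop the teleSCI arm's own hospital visits and calls, drop usual care's calls, and give up the comparison that randomisation protects.

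The arms differ by design in how often contact takes place, so a cheaper session need not mean a cheaper arm. Saving money and time is a stated hypothesis, and the Discussion expects the economic evaluation to settle whether teleSCI has economic benefits. A saving reported per session, or without equipment and support, would not answer that question.

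**Working it through.** **Figures in the plan.** The article states no cost figure, so there is none to reproduce. Its one computed design figure, 25 per group, does reproduce with two-sided alpha 0.05 (assumed): 2 × (1.960 + 0.842)² / 0.8² = 24.5, rounded up to 25. Nothing below depends on it.

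**Contrast against arms.**

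| Source | Telemedicine side | Comparator side |
|---|---|---|
| Statistical analysis | treatment via telemedicine | treatment at the hospital |
| The teleSCI group; The usual care group | video + hospital + telephone | telephone + clinic, on request |
| Methods/design | teleSCI group | usual care group |

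Rows two and three fit together. Row one fits neither, unless it is read as shorthand for the arms.

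**Scheduled contact.** Sessions every second or third week for at most 52 weeks (Table 2) give 52/3 = 17.3 to 52/2 = 26 per participant if the ulcer does not heal. Usual care has no stated number.

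**When a cheaper session gives a cheaper arm (illustration).** Set a hospital visit at cost 1. Let r be the relative cost of a video session, s the number of sessions, and E the equipment, set-up and support cost per participant in visit-equivalents. Let d be the number of extra hospital visits per participant in usual care over the teleSCI arm. Telephone use is taken as equal in both arms. The teleSCI total is lower only if

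d > s × r + E.

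The values of r and E are assumptions; the article gives neither.

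| r | Apparent saving per session (1 − r) | Break-even d, E = 0 | E = 1 | E = 3 |
|---|---|---|---|---|
| 0.25 | 75% | 4.3–6.5 | 5.3–7.5 | 7.3–9.5 |
| 0.50 | 50% | 8.7–13.0 | 9.7–14.0 | 11.7–16.0 |
| 0.75 | 25% | 13.0–19.5 | 14.0–20.5 | 16.0–22.5 |

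The second column only restates r: it stays the same however many sessions are held. The other columns depend on volume. With E = 0 the break-even is one extra usual-care hospital visit every 2/r to 3/r weeks: 8–12 weeks at r = 0.25, 4–6 at 0.50, 2.7–4 at 0.75. If follow-up ends earlier in both arms, s falls in proportion and this rate is unchanged, but E is spread over fewer weeks.

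**Cost list against resources used.**

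| Resource | In the Secondary endpoints list? |
|---|---|
| Number of teleSCI, hospital and telephone contacts | yes |
| Time per consultation, caregivers present, caregiver travel | yes |
| Lost work, medication, bandages, CO2 | yes |
| Webcam, project laptop, software, clinic video equipment | no |
| Installation and user training | no |
| Technician and nurse technical support | no; problems are logged, but no cost is attached |

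The three unlisted rows arise only under teleSCI.

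**The case against.** The strongest reply is that the by-arm comparison is already stated. Methods/design names the two groups and cost-benefit together. The Abstract uses the same hospital-versus-telemedicine shorthand and then labels the groups usual care and teleSCI, so the analysis sentence may be no more than that shorthand. It also speaks of treatment, not of consultations. This largely stands, and it limits the first part to inconsistent wording. It does not make the analysis sentence harmless, because that is the sentence an analyst follows.

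Second, the words "In the cost-benefit form we will ask for time used at each consultation" describe data collection, not a unit of analysis, and the form also records total consultations per participant in all modes. That stands: totals by arm can be built for the listed items. A reader might infer that teleSCI's own costs are left out altogether. The documents do not support this, since its sessions, time, caregivers and travel are recorded.

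Third, the full cost form is not shown, Table 1 names a cost-data tool, and Methods/design says technical logistics and service costs are mapped on forms at every assessment. Some missing items may be captured there. But recording at each assessment does not clearly reach one-off purchase, installation and training. The list also has no clinic-overhead line, so the net direction of everything unlisted cannot be settled from the article. What can be said is that omitting the teleSCI-only items lowers that arm's figure.

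Fourth, for the hypothesis that teleSCI shortens consultation time, time per consultation is a natural measure. That is a reason to report it, but not to let it stand for total time.

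**Conclusion.** The point holds in two limited parts. The Statistical analysis wording matches neither the randomised arms nor the two-group comparison in Methods/design, and should be reconciled with them. The itemised cost list omits equipment, software, installation, training and technical support, so a costing that followed it as written would understate teleSCI.

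A reader might go further and conclude that the analysis would favour teleSCI even if that arm cost more. The documents show only that this could happen. They give no unit costs and no usual-care visit counts, and the 17 to 26 sessions are an upper case that assumes no healing in 52 weeks. The break-even figures rest on assumed cost ratios, assumed fixed costs and equal telephone use; they illustrate the mechanism and do not estimate a bias. This is a secondary endpoint of a pilot trial, but one tied to a stated hypothesis and cheap to correct.

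**What to change.** Reword the cost sentence in the Statistical analysis section. The comparison should be mean total cost, and mean total staff and patient time, per participant by assigned arm. The period should be the trial follow-up, to healing or at most 12 months. This matches how data are collected: follow-up stops at healing and costs are recorded at each consultation, so a fixed 12-month horizon for everyone would need data the plan does not gather. Sum over all video, hospital and telephone contacts, give a confidence interval for the difference, and report cost or time per consultation as descriptive only.

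Add equipment, software, installation, training and technician time to the teleSCI arm, taken from project purchase and staff records.

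The change costs a little more costing work. Contact counts and consultation times are already on the form, and per Trial status data entry for the RCT was still to start in autumn 2018. The drawback for the investigators is that the teleSCI saving may look smaller.
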